### Secondary outcomes for the package intervention

- The proportion of high-risk individuals in the village that are identified and regularly managed by the village doctors. Regular management is defined as visiting the village doctor at least once a month, at least 9 times in a year, and measuring blood pressure and prescribing cardiovascular medicine during each visit
- The proportion of high-risk individuals who had visited the village clinic and received pharmaceutical treatment from the village doctor at least once in the past year
- The proportion of high-risk individuals that are treated with a blood pressure lowering agent
- The proportion of high-risk individuals that are treated with aspirin
- The proportion of high-risk individuals that have systolic blood pressure controlled to less than 140mmHg
- The proportion of high-risk individuals that report having received therapeutic lifestyle changes recommendations from the village doctors
- The mean blood pressure level of older adults (50+/60+) in the village
- The proportion of older adults with hypertension (systolic blood pressure >=140 mm Hg)

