### Baseline and follow-up surveys

A baseline and a follow-up random sample survey (2 independent samples) of older adults (50+/60+) will be conducted in all of the 120 villages before and after the interventions. In each village, the survey will collect data from 40 consenting adults, half men and half women. Sampling will be done by the China International Center for Chronic Disease Prevention located in Beijing acoording to village rosters collected before the survey. All age-eligible (50+/60+) villagers will receive a random number. The random numbers will be ranked according to ascending order and informed consents will be sought according to the rank orders until 20 men and 20 women in each village consent to participate in the survey. Efforts to make sure that only one older adult from the same household will be recruited in the survey will be made – through a roster including household information or someone (e.g. village chief) who knows the villagers well enough to identify adults from the same household. Blood pressure, weight, height and heart rate will be measured and recorded according to standardized protocol. A brief questionnaire (see Appendix 2) will be administered by survey staff to collect information on disease history, medication use, care seeking patterns, and lifestyle factors. Survey participants will receive a small gift valued at approximately 5 yuan (RMB) as a token of appreciation for their participation in the survey. Five yuan is approximately half of the minimal wage per hour for hourly workers.

High-risk patients in the evaluation surveys will be defined slightly differently from the high-risk definition in the package. It will be defined as having history of heart disease or stroke; or older age (50+/60+) and having diabetes; or older age (50+/60+) and having a measured systolic blood pressure > 160 mmHg; or older age (50+/60+) and currently on anti-hypertension medication but having ever had a self-reported BP measurement > 160 mmHg. See Appendix 2 for details on identification of high-risk patients from the random sample of older adults.

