| C.6 During the past 12 months, did you see your village doctor once a month?  □1. Yes  □0. No | | | | | | | | | C.7 Does your village doctor measure your blood pressure during visits?  □1. Never see village doctor  □2. Never measure  □3. Sometimes(occasionally)  □4. Almost every time  □5. Every time | | | | |
| **Physical examination (PE.2). Blood pressure and heart rate measurement (2nd)** | | | | | | | | | | | | | |
| PE.2.1 Blood pressure（Systolic/Diastolic）  PE.2.1.1**□□□**/ F.1.2**□□□** mmHg | | | | | | PE.2.2 Heart rate:  PE.2.2.1**□□□**/minute | | | | | | | |
| **Physical examination (PE.3). Body height and weight measurement** | | | | | | | | | | | | | |
| PE.3.1 Height **□□□.□** cm | | | | | | PE.3.2 Weight **□□□.□**kg | | | | | | | |
| | **CL．CVD high-risk patient confirmation checklist (CL) by the interviewer** | | | --- | --- | | CL.1 Have confirmed diabetes（C.1.1 answer Yes） | □1.Yes □0.No | | CL.2 Have confirmed stroke（C.2.1 answer Yes） | □1.Yes □0.No | | CL.3 Have confirmed CHD（Both C.3.1 and C.3.2 answer Yes） | □1.Yes □0.No | | CL.4 Have reported SBP at older age ≧ 160mmHg （C.5.1） | □1.Yes □0.No | | CL.5 Twice systolic measurements ≧160mmHg （PE.1.1 and PE.2.1） | □1.Yes □0.No | | **If any of the above is ticked YES, go to D section; otherwise, end survey** | | | | | | | | | | | | | | | |
| **D. Medication use and medical care (high-risk patients ONLY)** | | | | | | | | | | | | | |
| D.1 When was the last time that you saw your village doctor for your heart disease, stroke, diabetes or hypertension problem(s)? days ago  During that visit, did village doctor provide the following recommendations?  D.1.1 Reduce salt intake □1.Yes □0.No  D.1.2 Quit smoking □1.Yes □0.No  D.1.3 Avoid binge drinking □1.Yes □0.No  D.1.4 Be physically active □1.Yes □0.No  D.1.5 Control weight □1.Yes □0.No | | | | | | | | | | | | | |
| D.2 During the past 12 months, due to your heart disease, stroke, diabetes or hypertension problem(s)  D.2.1 How many times have you been in hospital?  （if no，go to D.3）  D.2.2 How many days have you been in hospital?  D.2.3 How much have you spent for hospitalization? RMB | | | | | | | | | | | | | |

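### The protocol text and the Appendix 2 checklist disagree on whether a person with a past high reading must be on treatment to count as high-risk, and the text rule lets the package change its own primary analysis population

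*Protocol*

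**What the plan says.** **Text.** The Protocol section on baseline and follow-up surveys lists four routes to high-risk status: a history of heart disease or stroke; qualifying age with diabetes; qualifying age with a measured systolic pressure above the threshold; and "older age (50+/60+) and currently on anti-hypertension medication but having ever had a self-reported BP measurement > 160 mmHg". It then refers the reader to Appendix 2 for details.

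**Survey form.** The Appendix 2 checklist has its own item for past readings, "CL.4 Have reported SBP at older age ≧ 160mmHg", with no medication condition. The routing rule is "If any of the above is ticked YES, go to D section; otherwise, end survey". Medication is first asked in the next block, headed "D. Medication use and medical care (high-risk patients ONLY".

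**Use.** The Outcomes section makes the mean blood pressure of high-risk patients the package primary outcome. Six of the eight package secondary outcomes use the same group, including "The proportion of high-risk individuals that are treated with a blood pressure lowering agent". High-risk status also underlies the power assumption of 8 in 40 and the urine sub-sample strata.

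**Timing.** The two surveys are independent samples, so high-risk status at follow-up is determined after two years of intervention. By contrast, the high-risk definition in the package section applies irrespective of medication.

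**The concern.** An untreated man of 60 with a past reading of 165, a reading of 150 today and no cardiovascular disease or diabetes is high-risk on the form and not high-risk in the text. A treated man of 55 whose only high reading came at age 45 is the reverse: the text places no age limit on the past reading, whereas CL.4 does. Neither group contains the other.

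This is more than a wording problem because the text's extra condition is current treatment, which the package is designed to increase. At follow-up, a package village that starts treatment in someone with a past high reading and a current reading below 160 brings that person into its high-risk set. The same person in a control village, left untreated, stays out. Those who enter this way have current pressures below 160, so the intervention arm's mean can fall even if treatment does nothing to blood pressure. The Analysis Plan compares the arms after the intervention, so such a shift goes straight into the primary contrast.

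**Working it through.** **1. Count in the protocol.** 8/40 = 20%, and 8 × 120 = 960, as the Statistical Power section states. That section does not say which definition the 20% refers to.

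**2. The conflicting route, side by side.**

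| | Survey section, fourth route | Checklist CL.4 |
|---|---|---|
| Past reading | ever | at qualifying age |
| Current medication | required | not considered |
| Applicable when the person is classified | no, medication is not yet asked | yes |

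**3. Size, under assumptions.** The protocol gives no stratum sizes, so all inputs here are assumed. Per 100 older adults:
- A = 10 to 20 people are high-risk by another route, with mean SBP 160.
- B = 5 to 10 people have only a past reading of 160 and measure below 160 now, with mean SBP 142.
- The treated share is 30% in control and 50% in intervention, in both strata.
- Treatment has no effect on blood pressure, so any shift in the mean comes from membership alone.

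Formulas, with t the treated share:
- Text denominator: A + B·t
- Text mean SBP: (160·A + 142·B·t)/(A + B·t)
- Text treatment rate: (A·t + B·t)/(A + B·t)
- Checklist denominator: A + B
- Checklist mean SBP: (160·A + 142·B)/(A + B), which does not contain t
- Checklist treatment rate: t

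Example with A = 15, B = 10:
- Control mean: (2400 + 426)/18 = 157.0.
- Intervention mean: (2400 + 710)/20 = 155.5, a shift of −1.5 mmHg.
- Checklist mean: (2400 + 1420)/25 = 152.8 in both arms, a shift of 0.

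| A, B | Text denominator, control → intervention | Shift in mean SBP (mmHg) | Text treatment rate, control → intervention | Contrast (points) |
|---|---|---|---|---|
| 20, 5 | 21.5 → 22.5 | −0.74 | 34.9% → 55.6% | 20.7 |
| 15, 5 | 16.5 → 17.5 | −0.94 | 36.4% → 57.1% | 20.8 |
| 20, 10 | 23 → 25 | −1.25 | 39.1% → 60.0% | 20.9 |
| 15, 10 | 18 → 20 | −1.50 | 41.7% → 62.5% | 20.8 |
| 10, 10 | 13 → 15 | −1.85 | 46.2% → 66.7% | 20.5 |

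Only the ratio of A to B matters for the means and rates, so 10 and 5 gives the same result as 20 and 10. Against the design difference of 2.5 mmHg the shift is 0.74/2.5 = 30% to 1.85/2.5 = 74%.

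**4. Treatment-rate contrast under other inputs.** The true difference is again 20 points.
- Treatment from 20% to 40% in both strata: the text contrast is 22.1 to 23.8 points for the last four rows of the table.
- Treatment from 30% to 50% in A and from 50% to 70% in B: 17.3 to 19.5 points for the same rows.
- Equal treatment in both arms: exactly 0.

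**The case against.** **Most differences between text and checklist are detail, not conflict.** This stands. A reader might infer that the two disagree on nearly every route: "Have confirmed CHD" needs a county-level diagnosis and ECG evidence, stroke and diabetes need hospital confirmation, and "Twice systolic measurements" requires both readings. But the text sends the reader to Appendix 2 for details and does not fix a number of readings. These items can fairly be read as the details it promises. Nor should the point rest on a strict against a non-strict threshold sign, since such signs are not reliable in the extracted text. Only the medication condition, and the smaller matter of a reading at any age against one at the qualifying age, cannot be read as elaboration.

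**The fourth route has a sound purpose.** It retains people whom treatment has brought below 160, and losing them would bias against the package. This is true, but CL.4 retains the same people if their high reading came at the qualifying age, and it does so without requiring treatment.

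**The data can be repaired afterwards.** This is largely right for this route. CL.4 combined with the medication questions identifies the text group, apart from treated people whose only high reading came before the qualifying age. But being able to derive either set does not settle which is primary, and choosing after follow-up data are in hand is what a fixed definition should prevent.

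**The sizes are invented.** The stratum sizes, means and treatment shares are assumptions. They show that the shift can be material, not what it will be.

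**Conclusion.** The contradiction is real and concerns the package's primary analysis population. The text's fourth route conditions on treatment; the form used to classify people does not. Under the text rule, membership at follow-up depends on what the intervention changes. With the assumed strata this alone moves the high-risk mean by −0.74 to −1.85 mmHg, against a design difference of 2.5 mmHg; under CL.4 the medication-driven shift is zero.

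A reader might go further and infer that the treatment-rate outcome is invalid because treatment is built into its denominator. The documents do not support that. Treatment is a condition of one route in four. The level of the rate is inflated, from 30% to about 35% to 46%, but the contrast stays within one point of the true 20 when treatment rises from 30% to 50%, and within about four points in the other cases tried. Where treatment is equal in the arms, no spurious difference arises. The main harm is to the primary outcome.

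**What to change.** - In the Protocol section on baseline and follow-up surveys, delete the current-medication condition from the fourth route and limit the past reading to the qualifying age, as CL.4 does.
- State that the high-risk set at both surveys is defined by checklist items CL.1 to CL.5. Write the hospital-confirmation, ECG and two-reading requirements into that section so that text and form match.
- State that treatment status is never a condition of entry to the high-risk set.
- Correct the label in the questionnaire: CL.1 refers to item C.1.1, which is printed as D.1.1.

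**Cost.** One paragraph of wording and one label; the form already collects every item.

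**Downside.** CL.4 still requires that blood pressure was measured at the qualifying age and that the person recalls it. The package can increase both, so some post-randomisation selection remains and should be acknowledged. Treated people whose only high reading came before the qualifying age would no longer enter by this route.

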### 24-hour urinary sodium

A 20% random sample (8 persons), stratified to have 4 from high-risk individuals and 4 from none high-risk individuals, will be selected from the survey participants to collect 24-hour urine. It will give a subsample of 960 participants, 480 in intervention and 480 in control. All urine in a 24-hour period will be collected for these participants, the volume will be recorded and a sample will shipped to a central lab for assays of sodium, potassium and creatinine according to standardized operating procedures. A freezer with-20ºC will be used to store the urine samples before shipping to the central lab in Beijing.

### Mortality and morbidity surveillance system

All village doctors including those in the control group will be required to record and report all deaths and fatal and non-fatal cardiovascular events. Non-fatal events will be collected using the modified WHO MONICA study protocol for acute coronary heart disease and stroke events. All data on non-fatal, hospitalized, and fatal cardiovascular events from the county emergency and hospitalization records (including township healthcare centers if possible) and all deaths from the Public Security Bureau (and/or County Centers for Disease Control and Prevention) death registrations will be used to confirm diseases and causes of death. With sufficient funding, personnel, and training, the “verbal autopsy” method will also be used to assign causes of death. All events will be reported to the central database in Beijing and be adjudicated by an independent adjudication committee.

### Case management records

These records are an integral part of the cardiovascular disease prevention and control package in the management of high-risk patients in the 60 intervention villages. In addition, these records will also provide a large amount of clinical information for better evaluation of the effects of the intervention and better understanding of the mechanisms and processes through which the package exerts its impacts. Such understanding is crucial for future improvement of the package and its widespread adoption.

### Village doctor survey

In order to assess whether the doctors in the intervention and control groups have comparable characteristics, we will collect basic information such as gender, date of birth, education, income, marital status, and years of clinical practice through a very short survey (see Appendix 3) for all the village doctors in the study. This survey will be conducted before the baseline village older adult survey but after obtaining their informed consent to participate in the study. In the case that they choose not to participate in the study even after group consent has been obtained from village leaders, we will select another village in the same township until we find consenting doctors and will conduct the village doctor survey and baseline older adult survey in the consenting village. The village doctor survey will be conducted only once at baseline; no follow-up survey is necessary.

## PROCESS EVALUATION

Aside from a comprehensive outcome evaluation, a process evaluation is also important.[49] The information on how the program is performed can help the investigators to understand the extent to which the program is implemented as planned and explain the outcomes.[50] Data will be collected by study personnel through surveys at baseline, during, and after intervention of all consenting village doctors on their healthcare knowledge and practice patterns. For the doctors in the “package” intervention program, a more in-depth survey of specific questions related to the program implementation at the end of intervention will also be conducted. For both the package and salt reduction interventions, interviews and focus groups at the end of the intervention will be conducted among key stakeholders involved in the programs including county officials, township health care center leaders, village doctors, community health educators, and villagers.

## ECONOMIC EVALUATION

An economic evaluation will provide an assessment of the cost-effectiveness of each of the intervention strategies. The perspective to be adopted will be that of the health sector and will include:

- Costs to government in establishing and running the program including the costs associated with the provider financial incentives. These data will be extracted from financial statements from the project and partner organizations (e.g. hospitals and village clinics). Adjustment will be made to exclude protocol driven costs associated with conducting research
- Associated costs to individuals and government of medical treatment and medications and the potential cost offsets associated with reductions in illness. Data on use of health care services and medications will be extracted from individual patient follow-up interviews. These resource items will be costed at standard prevailing market rates – recognizing variation in such unit costs across regions. Average costs per individual in each of the intervention groups will be estimated over the period of follow-up.

Cost effectiveness will be assessed initially in terms of cost per unit reduction in blood pressure for high-risk patients (package) or for older-adults (salt). However, additional modeling will be conducted to:

- Account for change in program costs associated with the scaling up of the intervention e.g. economies of scale through rationalization of upfront costs
- Extrapolate these trial based cost effectiveness findings into estimates of cost per life year saved and cost per Disability Adjusted Life Year (DALY) averted. These estimates will be based on evidence from the literature of disease progression and long term treatment effects.

These findings will enable the cost-effectiveness of the interventions tested in this study to be benchmarked against standard criteria such as that of the World Health Organization of a cost per DALY averted of less than three times gross national income.[51] Sensitivity analyses will be conduced to assess uncertainty in study findings associated with variation in study parameters.

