## THE CHINESE RURAL POPULATION AND HEALTHCARE SYSTEM

The majority of the 1.2 billion Chinese population live in rural areas.[8] China has 33 provincial administrations including 283 cities and 2859 rural counties.[9] Each county is further divided into about 15 townships (average township population size = 20000) and each township, in turn, comprises between 10 and 20 villages (average village population size = 1500). The rural healthcare system has a 3-tiered structure that mirrors the broader administrative organization of rural China - at the county level there are county hospitals and county centers for disease prevention and control, at the township level there are township community healthcare centers, and finally beneath that the village clinics (or healthcare stations).[8] The village clinics are administered and receive technical support from the townships and the townships are, in turn, administered and supported by the county Bureau of Health, comprised of the county hospital and county centers for disease control. On average in rural China there are 1.2 health care workers per 1000 residents, with the village primary care providers comprising a substantial proportion.

In each village, there is usually at least one primary care provider, a licensed village doctor who typically has received a limited professional training after completing high school. Most of the village doctors have prescription rights for basic medicines on the national essential drug list. The village clinics, themselves, are typically one or two dedicated rooms although most will contain only very limited medical equipment. In some villages, the village doctor is assisted by another healthcare worker, usually a woman, who has responsibility for maternal and child health and health education. The primary care providers and other healthcare workers live in the villages and work part-time with a modest salary provided by the county government; many work primarily in private practice although in some developed rural areas they may be full-time employees of the township government. Most consultations and subsequent care will require additional out-of-pocket payments by the patient to the primary care provider.

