### Amendments and additional submissions

Amendments to the protocol, participant information sheet or consent form will be submitted to the ethics committee for approval. Such amendments will only be implemented once ethical approval has been obtained, unless an amendment is being made to eliminate immediate hazards to study participants, which is highly unlikely in this study.

Certain components of this study are not determined at this time or will be informed by the results of the initial phase of the study; thus are not available in this protocol. These include details on

- The salt reduction intervention
- Process evaluation
- Economic evaluation
- Morbidity and mortality surveillance
- Procedures to conduct quality audit of the case management records
- Other measures (if undertaken) to ensure study quality

Additional new submissions for these components will be made at a later date when they are ready.

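### The cost-effectiveness benchmark is set at three times gross national income, a whole-country total, so any positive estimated health gain would meet it

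*Protocol*

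**What the plan says.** The Economic Evaluation section of the protocol works in two stages. The first is a trial-based ratio: cost per unit reduction in blood pressure, for high-risk patients (package) or older adults (salt). The second extrapolates the trial findings by modelling into "estimates of cost per life year saved and cost per Disability Adjusted Life Year (DALY) averted". The findings are then to be "benchmarked against standard criteria such as that of the World Health Organization", and the criterion given is that of the "World Health Organization of a cost per DALY averted of less than three times gross national income". The section gives no amount and does not say per person or per capita. It ends with sensitivity analyses intended to "assess uncertainty in study findings associated with variation in study parameters".

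Two other places bear on the point. The section on the rural population and healthcare system gives the size of the country: "The majority of the 1.2 billion Chinese population live in rural areas". The section on amendments and additional submissions says "Certain components of this study are not determined at this time" and lists the economic evaluation among the parts whose details will follow.

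**The concern.** The two sides of the comparison are on different scales. A cost per DALY averted is the price of one year of healthy life for one person. Gross national income is what a whole nation earns in a year. Setting the first below three times the second excludes nothing that a health programme could produce.

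The protocol's overall goal is to find effective, low-cost and sustainable interventions for wide implementation in rural China. This benchmark is the only numerical yardstick in the protocol for value for money. If the sentence is carried unchanged into the economic submission, a statement that an intervention meets the benchmark would carry no information about its value.

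**Working it through.** The benchmark is a quoted criterion, so the plan has no calculated figure to reproduce. The check is on its scale.

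**Inputs from the protocol.** Threshold: three times gross national income (Economic Evaluation). Population: 1.2 billion (rural population and healthcare system). Target difference in systolic pressure: 2.5 mmHg for each intervention (Statistical Power).

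**Step 1: ratio of the two thresholds, with no income figure needed.** Let y be income per person. Total income is 1.2 × 10⁹ × y.
- As written: 3 × 1.2 × 10⁹ × y = 3.6 × 10⁹ × y per DALY.
- Per person: 3 × y per DALY.
- Ratio: 1.2 × 10⁹, for any y.

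**Step 2: an extreme case, also free of assumptions.** A programme with cost C and D DALYs averted (D > 0) passes when C/D < threshold, that is, D > C/threshold. Let C equal the whole national income.
- As written: D > 1/3 DALY.
- Per person: D > 1.2 × 10⁹ / 3 = 400 million DALYs.

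**Step 3: a realistic scale, on assumptions.** The protocol gives no income per person, extra cost or DALYs per mmHg. Assumed ranges: income 5,000 to 50,000 yuan per person; extra cost 50 to 500 yuan per person; 0.0005 to 0.005 DALY averted per mmHg per person.

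| Income per person (yuan) | Per-person threshold (yuan per DALY) | Threshold as written (yuan per DALY) |
| --- | --- | --- |
| 5,000 | 15,000 | 1.8 × 10¹³ |
| 50,000 | 150,000 | 1.8 × 10¹⁴ |

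Cost per DALY at the protocol's 2.5 mmHg is cost / (DALY per mmHg × 2.5):
- most favourable: 50 / (0.005 × 2.5) = 4,000 yuan;
- least favourable: 500 / (0.0005 × 2.5) = 400,000 yuan.

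The per-person thresholds (15,000 to 150,000) fall inside this range, so a per-person benchmark would let some results pass and others fail. The lower written threshold is 1.8 × 10¹³ / 400,000 = 45 million times the least favourable result.

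**Step 4: smallest effect that passes, at the least favourable cost and DALY values.** Effect > 500 / (0.0005 × threshold).
- As written, lower income: 500 / (0.0005 × 1.8 × 10¹³) = about 0.00000006 mmHg.
- Per person: 500 / (0.0005 × 15,000) = 66.7 mmHg at the lower income, and 500 / (0.0005 × 150,000) = 6.7 mmHg at the higher.

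**Step 5: sign of the ratio when net cost is positive.** D > 0 gives a positive ratio, which passes as written. D = 0 gives an undefined ratio, which does not pass. D < 0 gives a negative number that is no longer a cost per DALY averted. The section has no sentence on the last two cases.

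**The case against.** The strongest reply is that this is a slip of two words in a sentence that binds nobody. The criterion is introduced as an example of standard criteria. No hypothesis, success decision or rollout decision refers to it. Details of the economic evaluation are openly deferred. The literal figure is so large that an economist would notice, go to the cited reference and use a workable threshold. Most of this stands, and it is why the point is minor. It does not make the sentence right. The threshold sits in the operative section, not in background text, and the later submission could repeat it. The planned sensitivity analyses vary study parameters, not the threshold, so they would not expose the problem.

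A reader might go further and infer that an intervention with no effect, or a harmful one, would be declared cost-effective, or would be so in all or nearly all trials. The documents do not support that.
- Zero effect gives an undefined ratio, which does not pass.
- Counting a negative ratio as a pass ignores that both measures are worded in terms of DALYs averted and of a reduction in blood pressure.
- Effectiveness is judged elsewhere, by hypotheses on blood pressure that expressly ask for a larger than usual effect.
- Any pass rate under a realistic threshold depends on income, cost and DALY figures that the protocol does not give.

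Methods for uncertainty in the ratio, price year and currency can properly wait for the later submission. Their absence is not an error.

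**Conclusion.** The threshold is wrong as written, and the severity is minor. It is 1.2 billion times a per-person threshold. That factor rests only on the protocol's own population figure and on reading gross national income as the national total that the term denotes. In practice every positive estimated health gain meets it, so the benchmark cannot discriminate. The yuan and mmHg figures only illustrate the scale and rest on the assumed ranges in the working; the conclusion does not depend on them. The primary outcomes, the hypotheses and the blood pressure analyses are unaffected. What holds is that a positive estimate, however small, would fall below the threshold. It does not follow that an ineffective or harmful intervention passes.

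**What to change.** In Economic Evaluation, state the threshold as three times gross national income per capita, after checking the wording against the reference cited there. Add one sentence saying that the benchmark applies only when the estimated DALYs averted are positive. Carry both into the economic submission announced under amendments and additional submissions.

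The cost is two sentences of text, with no new data and no change to the trial's conduct. The one downside is that the benchmark becomes harder to meet, because it can then be failed.
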